There is a specific need for interventions designed by, and targeted at, middle-aged women for several reasons. Firstly, men and women have different patterns of alcohol use and different motives for consumption [3,8,9]. For example, women are lighter drinkers than men, and use alcohol to experience respite from their traditional female domestic and caring responsibilities. Further, most web-based interventions that are female-centric have been aimed at pregnant women or those of childbearing age, with the content heavily tailored to these specific groups and a particular focus on the harms of alcohol to unborn babies [10,11]. Lastly, it has been shown that tailoring interventions using co-design with a target population is particularly efficacious in ensuring the effectiveness of an intervention or program [12,13]; thus, an intervention designed by and for middle-aged women is likely to have amplified effectiveness.

To our knowledge, there are no web-based interventions targeted specifically at middle-aged women that have been documented in the literature. Our study aims to fill this gap by developing and testing the effectiveness of a web-based intervention in reducing alcohol consumption among women aged 40-65 years. The primary aim of this study is to test the effectiveness of a 3-arm web-based intervention in reducing both the frequency of alcohol consumption as well as the alcohol intake per occasion among middle-aged women. Secondary aims include testing the effectiveness of the intervention in increasing awareness of the long- and short-term harms associated with alcohol consumption, increasing motivation to reduce alcohol consumption, reducing alcohol-related harm, improving reported health status and mental health, and increasing social support. We will also test reactivity to the ecological momentary assessment (EMA) by comparing a control group with weekly assessment to a pre-post control group.

### Hypothesis 1

We hypothesize that by the end of the intervention period, participants in the web-based intervention group will report significantly lower alcohol consumption compared with participants in the pre-post control group (H1).

### Hypothesis 2

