We hypothesize that by the end of the intervention period, participants in the web-based intervention group will display significant increases in their awareness of harms associated with alcohol consumption (H2a), their motivation to reduce their alcohol consumption (H2b), social support (H2c), and current health status (H2d); they will also display significant decreases in alcohol-related harm (H2e) when compared to the pre-post control only group.

### Hypothesis 3

We hypothesize that by the end of the intervention period, participants in the control group with weekly assessment will have greater reductions in alcohol consumption compared with participants in the pre-post control group (H3a). We further hypothesize that participants in the intervention group will report a greater reduction in alcohol consumption compared with participants in the control group with weekly assessment.

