### Sample Size Calculation

The effect sizes obtained in brief interventions, that is, change in the intervention group compared to the control group, are usually relatively small [4]. Power analyses in the statistical software G*Power 3.1.9.4 [14] were conducted to determine the power (probability) to successfully find differences between the intervention group and the 2 control groups. In this study, we aim to recruit 3000 participants. However, we may be short on this aim by one-third and have one-third attrition leaving us with a sample of 1333. Using repeated measures ANOVA with within-between interactions (ie, 2 measurements over time [pre-post assessments; note that in any case the EMA assessments will have a higher test power] interacting with the membership in 1 of 3 groups), this reduced sample will still have a power (probability) of more than 99% to detect even small effect sizes (*P*=.99; [15]) with an α-error threshold of .001. In other words, the intended sample size is sufficient to test all hypotheses successfully.

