### Data Analysis

The reporting and presentation of this trial will be in accordance with the CONSORT (Consolidated Standards of Reporting Trials) guidelines for randomized controlled trials, and data on screening, refusals, and dropout will be coded and reported on per the guidelines [33]. The comparative analysis will be analyzed in accordance with the intention-to-treat principle and the completers-only framework. Participants will have to sign up to the intervention and complete approximately 30% of the EMA surveys to be considered for inclusion in the analysis; missing data will be handled accordingly. The intention-to-treat analyses’ multiple imputation methods will be used, while completers-only analyses will be conducted on participants providing scores for all measurements.

All data that are collected will be analyzed using statistical software packages such as STATA (StataCorp) and Mplus (Muthén & Muthén). ANOVAs, contrasting the intervention groups against both control groups, will be run, and logistic and linear regression models will be used to determine potential influencing variables. Longitudinal analyses will be conducted to test group differences in EMA assessments over time.

Besides testing the main effects of the intervention, moderating effects of age, drinking status (whether participants are “risky” drinkers according to the Australian Alcohol Guidelines [34]), educational status, and presence of dependent children in the household will be investigated to establish whether specific subgroups are more likely to benefit from the intervention.

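### Omnibus power of more than 99% does not show that the sample suffices for every pairwise hypothesis, and Data Analysis leaves the contrasts open and omits the one for H3a

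*Protocol article*

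**What the plan says.** The Introduction of the protocol article sets out comparisons between pairs of arms.

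- Hypothesis 1: "participants in the web-based intervention group will report significantly lower alcohol consumption compared with participants in the pre-post control group (H1"). Hypothesis 2 uses the same pair for the secondary outcomes.
- Hypothesis 3, first part: "participants in the control group with weekly assessment will have greater reductions in alcohol consumption compared with participants in the pre-post control group (H3a").
- Hypothesis 3, second part: a greater reduction with the intervention than in the control group with EMA.

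The aims at the end of Background also announce that reactivity to EMA will be tested by comparing the two control groups.

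Sample Size Calculation starts from a target ("In this study, we aim to recruit 3000 participants") and reduces it: "we may be short on this aim by one-third and have one-third attrition leaving us with a sample of 1333". The power model is described as "Using repeated measures ANOVA with within-between interactions", with two measurements "interacting with the membership in 1 of 3 groups". It reports that "this reduced sample will still have a power (probability) of more than 99% to detect even small effect sizes" at an alpha of .001, and concludes from this that the sample is enough for every hypothesis.

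Data Analysis names the group comparison in one clause: "ANOVAs, contrasting the intervention groups against both control groups, will be run". It adds regression models for influencing variables and a longitudinal analysis of the EMA data.

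**The concern.** The interaction in the power calculation has 2 numerator degrees of freedom. Its null is that all three arms change equally, and it uses the whole spread of the three means. Each hypothesis concerns one pair of arms. High power for the spread does not give high power for a pair that is closer together, so the step from the omnibus figure to all hypotheses is not justified.

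The analysis clause has two gaps.

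- It does not say whether the intervention is compared with the average of the controls or with each control in turn. These are different tests when the controls differ, which is what H3a predicts.
- On neither reading are the two controls compared with each other. The longitudinal EMA analysis cannot fill this gap, because control group 1 is not contacted between baseline and the 8-week questionnaire (Comparator).

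At stake are the two comparisons that the third arm exists for: whether EMA alone lowers drinking, and whether the web content adds to EMA. A null result on either could be read as informative on the strength of a power figure that does not belong to it.

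**Working it through.** **Inputs from Sample Size Calculation.** Analysed N = 3000 × 2/3 × 2/3 = 1333; k = 3 groups; m = 2 measurements; alpha .001.

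**Assumptions, because the article gives no figure.** Small effect f = 0.10; pre-post correlation rho = 0.5 (range 0 to 0.7); 1:1:1 allocation, so 1333/3 = 444.3 per arm. H1 and H3 together predict the order intervention < EMA-only < pre-post control; equal spacing of the three is assumed.

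**Step 1: the plan's own figure.** The noncentrality is lambda = f² × N × m/(1 − rho), with 2 and 1330 degrees of freedom. At rho = 0.5 it is 0.01 × 1333 × 2/0.5 = 53.3, and power at .001 is 0.9999. At rho = 0.3 power is 0.9945 and at rho = 0 it is 0.939. With f = 0.05 and rho = 0.5 it is 0.52. The stated figure therefore reproduces with f = 0.10 and a correlation of about 0.3 or more.

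**Step 2: the same effect, pair by pair.** On change scores the effect is f × √(m/(1 − rho)) = 0.10 × √4 = 0.20. For means 0, −d, −2d the standard deviation of the means is d × √(2/3), so d = 0.20/0.8165 = 0.245 SD of change.

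- Standard error of a pairwise difference: √(2/444.3) = 0.0671.
- Adjacent arms (H3a; intervention against EMA-only): z = 0.245/0.0671 = 3.65. The two-sided critical value at .001 is 3.29, so power = Φ(0.36) = 0.64. At .05 it is Φ(3.65 − 1.96) = 0.95.
- Outer arms (H1): z = 7.30, power above 0.999.

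| rho | Interaction, .001 | H1, .001 | H3a, and intervention vs EMA-only, .001 | Same, .05 |
|---|---|---|---|---|
| 0 | 0.94 | 0.97 | 0.24 | 0.73 |
| 0.3 | 0.99 | 0.998 | 0.42 | 0.87 |
| 0.5 | >0.999 | >0.999 | 0.64 | 0.95 |
| 0.7 | >0.999 | >0.999 | 0.92 | 0.997 |

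Over the correlations that reproduce the stated figure (0.3 to 0.7 in this table), the two adjacent comparisons have 42% to 92% power at .001.

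**Step 3: what depends on the reading of the contrast.** Suppose EMA lowers drinking and the web content adds nothing, so that intervention and EMA-only share the same mean change −d. A pooled contrast then estimates d/2, with standard error √(1.5/444.3) = 0.0581.

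- At f = 0.10 and rho = 0.5, d = 0.20/√(2/9) = 0.424. Then z = 0.212/0.0581 = 3.65, and the pooled contrast rejects 64% of the time at .001 and 95% at .05.
- With a smaller reactivity of 0.2 SD of change, z = 0.1/0.0581 = 1.72, giving 6% at .001 and 41% at .05.
- The direct test of intervention against EMA-only stays at its nominal alpha in both cases.

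**The case against.** A reader might infer that the stated tests have the wrong null hypotheses and that the trial will be decided by a test that can reject for the wrong reason. The article does not support that.

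- The comparison with both controls can equally mean two separate contrasts. Their nulls are then exactly those of H1 and the second part of H3. The pairwise wording of the hypotheses, and the reason that Strengths and Limitations gives for having two control groups, favour this reading. The rejection rates in Step 3 apply only if the controls are pooled.
- The three-group interaction appears only as the basis of the power calculation. Data Analysis does not name it as the deciding test.
- H3a is not forgotten: the aims announce the comparison of the two controls, and both arms supply baseline and 8-week data, so it can be done.
- A full list of contrasts may stand in an analysis plan that is not shown, and its absence from an article would not be a fault by itself.

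These four objections stand, and they limit the second half of the point to an ambiguity and an omission in a clause that does name contrasts. They do not touch the power inference, which the article asserts.

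Two further defences bear on the size. At alpha .05 the adjacent comparisons have about 95% power at correlation 0.5; but .001 is the only threshold that the article attaches to its claim. With the full 3000 analysed (1000 per arm), z = 0.245/√(2/1000) = 5.48 and power at .001 is Φ(2.19), about 99%; but the article draws its conclusion from the reduced sample of 1333.

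**Conclusion.** The power stated for the omnibus interaction does not show that the sample is sufficient for all hypotheses. With f = 0.10, 1:1:1 allocation, equally spaced arms, N = 1333 and alpha .001, H3a and intervention against EMA-only each have about 64% power at correlation 0.5, and 24% to 92% over correlations 0 to 0.7. H1, the primary comparison, remains well powered under the same assumptions. Effect size, correlation, allocation and spacing are all assumed, and the shortfall shrinks at alpha .05.

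Data Analysis also leaves open whether the controls are pooled, and does not carry through the EMA-only against pre-post comparison that the aims announce. If one pooled contrast were run, it could reject through EMA reactivity alone; the article does not say that this will be done. The point should be corrected, but it does not undermine the design.

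**What to change.** In Data Analysis, replace the clause on ANOVAs with three pairwise contrasts at 8 weeks, all from one model with three arm levels:

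- intervention against control group 1, for H1 and H2;
- control group 2 against control group 1, for H3a;
- intervention against control group 2, for the second part of H3.

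State that the two control groups are not pooled and that the omnibus group-by-time test is supportive only.

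In Sample Size Calculation, replace the inference to all hypotheses with the power of each pairwise contrast, and state the effect size, the pre-post correlation and the alpha behind it.

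The change is one of wording and needs no new data or participants. It has two costs. The stated power will look less favourable for two of the three comparisons. And if the two controls turn out to be equal, a pairwise test has somewhat less power than a pooled one: at 0.2 SD, 444 per arm and alpha .05, about 85% (z = 0.2/0.0671 = 2.98) against 93% (z = 0.2/0.0581 = 3.44).

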**Methods:**

The study is a 3-arm randomized controlled trial with a web-based intervention plus ecological momentary assessment (EMA) group compared to an EMA-only and a pre-post only control group. The study is aimed at middle-aged women, defined as women aged between 40 and 65 years, who consume alcohol at least weekly or who have consumed 4 or more drinks on 1 occasion in the last month. The intervention aims to reduce alcohol consumption through 4 modules that provide information on the health impacts of alcohol, mindfulness, social influences, and alcohol marketing. Intervention participants will also fill out biweekly EMA assessments. The comparators are EMA-only and pre-post control only. The primary outcome is alcohol consumption at 8 weeks compared between groups. Secondary outcomes are awareness of alcohol-related harms, readiness to change alcohol consumption, health status, mental health, and social support.

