#### Alcohol-Related Measures

##### Typical Drinking (Baseline and Follow-up)

Participants will also be asked to report on how much they typically drink each day of the week (eg, “How many drinks containing alcohol do you consume on a typical Monday?”)

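### The ANOVAs planned for the group comparisons are valid but less precise than a baseline-adjusted model, which would need no new data

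*Protocol article*

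**What the plan says.** The abstract describes the main comparison as follows: "The primary outcome is alcohol consumption at 8 weeks compared between groups". The Outcomes section names two primary outcomes, how often women drink and how much they drink per occasion.

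Under Data Analysis, the method for the arm comparison is "ANOVAs, contrasting the intervention groups against both control groups, will be run". Regression is given another task: "logistic and linear regression models will be used to determine potential influencing variables". The longitudinal analyses in the same section concern the EMA data. Control group 1 does not provide EMA data, so those analyses cannot serve H1 or H3a, both of which compare against that group.

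The Sample Size Calculation section is more specific about the form of ANOVA: "Using repeated measures ANOVA with within-between interactions", with "2 measurements over time [pre-post assessments" and "interacting with the membership in 1 of 3 groups".

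Baseline data are available throughout. Under Procedures, all three arms complete baseline and follow-up questionnaires, and randomization takes place only after the baseline survey is finished. Consumption is asked at both times. Under Typical Drinking (baseline and follow-up) the article says "Participants will also be asked to report on how much they typically drink each day of the week", and the daily consumption measure is also listed for both. Nowhere is baseline consumption named as a covariate in the arm comparison.

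**The concern.** A woman's drinking before randomization will usually tell something about her drinking eight weeks later. A follow-up-only ANOVA makes no use of that information. A two-time-point repeated-measures ANOVA does use it, but it subtracts the whole baseline value whatever the correlation, which over-corrects unless the correlation is close to 1. A model with baseline as a covariate estimates how much to subtract.

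What is at stake is the precision of the three pairwise contrasts behind H1 and H3. The article itself expects small effects, and it plans for the possibility of losing more than half of its recruitment target. The contrast for reactivity to EMA (H3a) may well involve one of the smaller effects.

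**Working it through.** **Inputs from the article.** Target: "we aim to recruit 3000 participants". A one-third shortfall followed by one-third attrition gives 3000 × 2/3 × 2/3 = 1333, as stated. There are three groups and two time points; alpha is .001 and stated power is above 99% for a small effect.

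**Assumed, because the article does not give them.** Equal allocation (1333/3, about 444 per arm); a small effect meaning f = 0.10 for the omnibus test and d = 0.20 for a pairwise contrast; rho of 0.3, 0.5, 0.7 or 0.8; equal variances at both times and the same rho in every arm.

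**Step 1: the plan's own figure.** For the time-by-group interaction in the default G*Power form, lambda = f² × N × m / (1 − rho). With f = 0.10, N = 1333, m = 2 and rho = 0.5, lambda = 0.01 × 1333 × 2 / 0.5 = 53.3. On 2 and 1330 degrees of freedom at alpha .001, power is 99.99% (99.45% at rho 0.3). The stated figure reproduces. It refers to the three-group interaction, not to a pairwise contrast.

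**Step 2: relative variance of an arm difference.**
- Follow-up-only ANOVA: 1
- Change score (two-time-point repeated-measures ANOVA): 2(1 − rho)
- Baseline-adjusted model (ANCOVA): 1 − rho²

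The share of participants saved by ANCOVA is rho² against the follow-up-only ANOVA. Against the change score it is 1 − (1 − rho²)/[2(1 − rho)] = (1 − rho)/2.

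| rho | Variance, change score | Variance, ANCOVA | Saved vs follow-up only | Saved vs change score |
|---|---|---|---|---|
| 0.3 | 1.40 | 0.91 | 9% | 35% |
| 0.5 | 1.00 | 0.75 | 25% | 25% |
| 0.7 | 0.60 | 0.51 | 49% | 15% |
| 0.8 | 0.40 | 0.36 | 64% | 10% |

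Both savings are positive for every rho strictly between 0 and 1.

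**Step 3: pairwise power.** Two-sided noncentral t at .05, with noncentrality d × √(n/2) / √(relative variance). With n = 444 and d = 0.20, d × √(n/2) = 0.20 × √222 = 2.98. At rho 0.5, for example, ANCOVA gives 2.98/√0.75 = 3.44.

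| rho | Follow-up only | Change score | ANCOVA |
|---|---|---|---|
| 0.3 | 84.5% | 71.1% | 87.7% |
| 0.5 | 84.5% | 84.5% | 93.0% |
| 0.7 | 84.5% | 97.0% | 98.6% |
| 0.8 | 84.5% | 99.7% | 99.9% |

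**Step 4: the more favourable sample.** If 3000 are recruited and one third drop out, 2000 remain, about 667 per arm. At rho 0.5 and .05, power is 95.5% for either ANOVA form and 98.8% for ANCOVA.

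**The case against.** The best defence is that the only ANOVA described in detail is the pre-post interaction, which does use baseline. On that reading, which is the natural one when the two sections are taken together, the loss is partial, and it shrinks as baseline becomes more predictive: at rho 0.8 there is almost nothing left to gain at .05. H3 is also worded in terms of reduction, which a time-by-group test addresses directly. And 1333 is a pessimistic case, not the expected sample. All of this stands, and it limits the size of the point.

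Two stronger readings are tempting, but the document does not support them. One is that the plan throws baseline away. That would be true only of a follow-up-only ANOVA. The abstract's wording allows that form, but no section specifies it. The other is that the planned tests are biased or invalid because of chance baseline imbalance. Under randomization both forms estimate the arm difference without bias, and chance imbalance is already reflected in their standard errors.

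It can also be said that regression is planned, that risky-drinking status is examined as a moderator, and that covariates are commonly left to an analysis plan. But neither use puts baseline consumption into the main contrasts. The article does name a method for those contrasts, and an analysis plan using ANCOVA would depart from it.

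**Conclusion.** The point holds as one of efficiency, not validity. The article commits the arm comparisons to ANOVA without baseline adjustment, although the baseline value is on record for every randomized woman. A baseline-adjusted model is more precise than either ANOVA form for any correlation between 0 and 1.

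The size of the gain depends on a correlation that the article does not give. Against the repeated-measures form, the gain in power in the 1333 case runs from about 17 percentage points at rho 0.3 (87.7 − 71.1 = 16.6) to 0.2 points at rho 0.8. Against a follow-up-only ANOVA the pattern reverses, from about 3 points (87.7 − 84.5 = 3.2) to about 15 (99.9 − 84.5 = 15.4). These figures rest on the assumed d = 0.20, equal arms and a .05 threshold for each contrast. The article's power statement is not wrong on its own inputs. This is a free improvement that should be made, not a defect that threatens the trial's conclusions.

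**What to change.** For each stated primary outcome (frequency of consumption, and intake per drinking occasion), make the primary analysis a regression of the 8-week value on randomized arm, adjusted for the baseline value of the same measure. Use robust standard errors, because drinking measures are usually skewed. Take the three pairwise contrasts from that one model: intervention against control group 1 (H1), control group 2 against control group 1 (H3a), and intervention against control group 2 (second part of H3). Keep the two primary outcomes as they are and do not merge them into one weekly total.

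Use the same baseline adjustment for secondary outcomes, with a model suited to the scale, for example an ordinal model for the single five-category health item.

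The cost is a change of wording in the Data Analysis section, dated and recorded before any analysis by arm. It needs no new data, contacts or participants. The sample size section can stay, with a note that the primary analysis is now the adjusted model.
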